### Additional analyses

GIS and socio-economic data are already being collected in the DSS and thus provide a good opportunity to undertake these analyses. In the control area, data analysis will also be done by doing a before-and-after comparison to estimate the effect of only health facility improvement on maternal and neonatal care facilities. Subgroup analyses estimating separate intervention effects for facility- and home-based deliveries.

Analysis will also be done taking account of the quality of the intervention received, as assessed by the process indicators and number of visits received. Because some study participants are highly mobile and some women will move from their place of residence to their parents’ or in-laws’ houses for delivery of the baby, it is envisaged that there may be significant movements across the arms of the trial (that is, some women will move from intervention to control areas and vice versa) during the intervention period. This movement can be tracked using our surveillance system. Thus we will also compare outcomes subdividing women and newborns into the following groups: whether the visits were only pre-delivery or only post-delivery or both, and whether the woman received all five visits, only four, three or two or less visits. However, the main analysis will be based on intention to treat so women who are enrolled in an intervention area, but move to a control area for delivery, will be included in the intervention group.

In addition, analysis will also be done of the mean practice score (a numerical outcome) will be carried out using random effects (multilevel) models that explicitly model the similarity between individuals in the same cluster; (these are not suitable for binary outcomes).

For all statistical determinations, significance levels will be established at 5% level of significance. Coefficient of variation will be reported.

While not a primary outcome, variable stillbirth rate and neonatal mortality rate will be followed through the study in both intervention and control areas. We will define miscarriage as cessation of a presumptive pregnancy before 28 weeks of gestation and stillbirth as fetal death after 28 weeks of gestation but before delivery of the baby’s head, which was a modification of the 22-week definition to meet local practicalities. We will classify neonatal death as death of a live born infant within 28 completed days of birth. Early neonatal deaths will refer to deaths within 7 completed days after delivery. Separate analysis will be done for neonatal mortality excluding the first day of life in order to assess the role of sepsis.

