**Methods/Design:**

Through formative research around evidence-based practices, and dialogue with policy and technical advisers, we constructed a home-based neonatal care package implemented by the responsible VHT member, effectively a Community Health Worker (CHW). This CHW was trained to identify pregnant women and make five home visits - two before and three just after birth - so that linkages will be made to facility care and targeted messages for home-care and care-seeking delivered. The project is improving care in health units to provide standardized care for the mother and the newborn in both intervention and comparison areas.

The study is taking place in a new Demographic Surveillance Site in two rural districts, Iganga and Mayuge, in Uganda. It is a two-arm cluster randomized controlled design with 31 intervention and 32 control areas (villages). The comparison parishes receive the standard care already being provided by the district, but to the intervention villages are added a system for CHWs to visit the mother five times in her home during pregnancy and the neonatal period. Both areas benefit from a standardized strengthening of facility care for mothers and neonates.

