### Overview of the trial design

#### Randomization

The unit of intervention and randomization was the village. The study area has 63 villages. All the 63 villages were eligible for randomization. Given the relatively large number of study units (63), we proposed not to stratify or match. Allocating 31 villages to intervention and 32 to comparison we thus have 31 units of intervention, each with 1 to 3 CHWs depending on the number of households therein (Figure 2). Given that the intervention is primarily through home visits by the CHW, we never anticipated contamination to be a big problem, since that would imply making extra home visits. This, however, would be monitored in the annual coverage surveys proposed. Spillover by word of mouth woman-to-woman or other would be captured as a secular trend in the comparison villages. Statistically, we believe it is advantageous to keep the unit of intervention and randomization the same. We also avoid the complexities of which outcome measure to match/stratify on.

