### Pathways to effect in intervention

If the educational components are successful in changing behaviours associated with risk in neonates, then the interventions should result in improvement in neonatal mortality (Table 2). Hopefully, the combination of improved health facility services and increased awareness and support at the community level, will result in greater compliance with pre- and postnatal care recommendations in a situation where the quality of the services holds minimum standards, thus involving components of both the ‘demand’ and ‘supply’ side. This is the model and assumption being tested in this study.

**Table 2 T2:** Proposed actions, targeted cause of death and behaviour

**Intervention**	**Cause of death addressed**	**Behaviour addressed**

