### Data analysis

The detailed analysis plan for the trial will be finalized during the evaluation preparation phase. For the qualitative study, content analysis will be used for data analysis and emerging themes arranged into categories. NVivo version software (QSR International, Melbourne Australia) will be used for the analysis.

Quantitative analysis of practice variables will use descriptive univariate analysis for all variables separately, then an intention-to-treat approach comparing summary variables in the intervention to control clusters. However, the effects of the health facility strengthening will be assessed in the control clusters using a ‘before-after’ approach. Outcomes will be compared with adjustment for clustering using appropriate Stata commands (svy). For 2×2 cross tabulations containing cells with expected frequencies of fewer than 5, statistical significance will be determined using Fisher’s exact test, the method consists of evaluating the sum of probabilities associated with the observed table and all possible 2×2 tables that have the same row and column totals as the observed data but exhibit more extreme departure from independence; Yates’ corrected chi square will be used for all others when testing for independence in a contingency table. For cross tabulations with greater than 2 rows, statistical significance will be determined using the Pearson chi square test.

Analysis of variance (ANOVA) will be used for statistical comparison of means. Randomized experiments suggest that ANOVA is particularly appropriate for the analysis of data from experiments in which each subject/individual in the experimental unit is randomly assigned to one of two or more different treatment conditions (control and intervention groups). All subjects in a particular group will receive the same treatment, and differences in the effects of the treatments (control and intervention) are expected to produce differences between groups in post-treatment scores on a relevant measure.

In midterm evaluation, in order to see who is and who is not receiving the intervention, we will carry out analyses using important criteria such as: reach/coverage (who is receiving and not receiving the intervention and what are their characteristics) (data to come from the surveys we are planning from ‘exposure to CHW intervention’ variable); and fidelity (the extent to which the intervention is delivered as originally defined.

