## Discussions

This study is an effectiveness study designed to directly influence policy. Therefore implementation will be done in close consultation with policy makers and there will be ongoing feedback with preliminary findings. In addition, we will also share the study materials with all interested parties even well before the final evaluation is made. There will be close documentation of all implementation steps, challenges, innovations and experiences occurring at both the demand and supply sides. In addition, the study will be costed as this is important for influencing the policy agenda.

The study has some limitations mainly related to lack of power to measure mortality impact. Another limitation is that the study is implemented in a small area where the risk of contamination is high.

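### The before-after change in control villages cannot be read as the effect of facility strengthening alone: it also contains secular trend and the spillover that the protocol itself places there

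*Protocol article*

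**What the plan says.** All references are to the protocol article.

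- **Who gets facility strengthening.** The abstract (Methods/Design) says: "Both areas benefit from a standardized strengthening of facility care for mothers and neonates". The section on the intervention lists health worker training and supplies for facilities in both arms. The section on health facility strengthening extends this to every facility in and around the study area.
- **How its effect is to be estimated.** Under Data analysis, "the effects of the health facility strengthening will be assessed in the control clusters" by a before-after approach. Additional analyses describes the same thing as a "before-and-after comparison to estimate the effect of only health facility improvement on maternal and neonatal care facilities".
- **Where spillover is expected to appear.** Under Randomization: "Spillover by word of mouth woman-to-woman or other would be captured as a secular trend in the comparison villages".
- **How likely contamination is.** Under Randomization: "we never anticipated contamination to be a big problem". Under Discussions, the study is said to be "implemented in a small area where the risk of contamination is high". Additional analyses also expects that movement of women between arms may be significant.

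**The concern.** The plan names a causal quantity, the effect of facility improvement and nothing else, and assigns it to an uncontrolled comparison over time. The same article says that spillover from the other arm will be part of that change over time. The two statements do not fit together.

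Two consequences follow. First, any rise in the control villages, whatever its cause, would be reported as a benefit of facility strengthening. The Discussions section says the study is meant to influence policy directly, and a claim about facility strengthening alone bears on what is scaled up. Second, describing spillover as captured in the comparison trend suggests that it has been handled. It has not: better practices in control villages reduce the difference between arms, so the CHW effect is understated.

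**Working it through.** The article gives no figure for this analysis, so there is none to reproduce. The question is what the planned comparison identifies.

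**Decomposition.** Write F for the facility effect, S for the secular trend over the study period, V for the effect of CHW visits in intervention villages, and C for spillover of the CHW intervention into control villages. Assume for simplicity that these add, and that F and S are the same in both arms.

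- Change in control villages = F + S + C
- Change in intervention villages = F + S + V
- Difference between arms = (F + S + V) − (F + S + C) = V − C

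The first line is what the plan would label F. It is one observed quantity with three unknowns. The third line does not help, because F cancels: both arms were strengthened. No unstrengthened group inside or near the study area is described. The third line also shows what spillover does to the main comparison. If C has the same sign as V, the difference between arms is smaller than V.

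**Illustration.** The baseline of 40% and the 20-point CHW effect are the protocol's own planning values for four antenatal visits. The trend values, the spillover shares and F = 0 are assumptions. Spillover of 0%, 10% or 25% of 20 points is 0, 2 or 5 points. The apparent facility effect is S + C:

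| Secular trend S (points) | C = 0 | C = 2 | C = 5 |
|---|---|---|---|
| 0 | 0 | 2 | 5 |
| 2 | 2 | 4 | 7 |
| 5 | 5 | 7 | 10 |
| 10 | 10 | 12 | 15 |

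So with no true facility effect, the plan's label would attach to anything from 0 to 15 points in this range. In the same cases the difference between arms would be 20, 18 or 15 points instead of 20.

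**Chance of a false positive.** Take the 7-point case, 40% to 47%, with k = 0.25 as the protocol states. For C clusters of m women per survey and correlation r between a cluster's before and after levels,

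variance = [p0(1 − p0) + p1(1 − p1)]/(Cm) + k²(p0² + p1² − 2·r·p0·p1)/C.

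With 9 clusters of 60 and r = 0: (0.2400 + 0.2491)/540 + 0.0625 × (0.1600 + 0.2209)/9 = 0.00091 + 0.00265 = 0.00355. The standard error is 0.0596, and a nominal 5% test rejects about 22% of the time. With r = 0.8 it rejects 45%. With 32 clusters of 15 it rejects 39% (r = 0) or 53% (r = 0.8). The layouts and r are assumptions; the protocol states neither. The rejection rates only illustrate the point, which rests on the decomposition.

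**The two statements on contamination.** Randomization reasons that the intervention works through home visits, so contamination would need extra visits. Discussions calls the risk high because the area is small. The first supports the choice of the village as the unit; the second is listed as a limitation. No sentence connects them.

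**The case against.** **It is only an additional analysis.** True. The before-after comparison is not among the stated hypotheses, and no primary conclusion rests on it. That limits the consequence but does not make the label correct.

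**Detail can wait for the analysis plan.** The article says a detailed plan will follow, and modelling choices can be left to it. The point here is not a missing detail: the article already fixes both the comparison and its causal reading.

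**Contamination is partly monitored.** This stands. Annual coverage surveys are to monitor it, the interview records exposure to CHW home visits, the surveillance system can track movement between arms, and contextual events are documented. None of this is tied to the before-after estimate, and recording visits would not detect word-of-mouth spillover.

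**The two contamination statements differ in scope.** Partly right. Randomization speaks of home visits and treats word of mouth separately, while Discussions speaks generally. The reader still meets a low and a high expectation with no reconciliation.

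**Dilution is conservative and the risk is disclosed.** Also fair, but the Randomization section describes spillover as captured, not as a bias with a direction.

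Two stronger readings are tempting.

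- *A reader might infer a collapse in power.* Holding the intervention arm at 60% while controls rise from 40% to 45% or 50% takes power from 0.85 to 0.58 or 0.29, with 9 clusters of 60 per arm and k = 0.25 (normal approximation). But strengthening reaches both arms. If it lifts both equally, the same formula gives 0.79 (45% against 65%) and 0.73 (50% against 70%). Nine parishes per arm is itself an assumption, and power of the randomised contrast does not measure this defect.
- *A reader might infer that the trial claims to test the combined package,* from "This is the model and assumption being tested in this study". That sentence closes a paragraph on the conceptual pathway. The abstract, the hypothesis and the Hypothesis testing section frame the test as CHW home visits added, by village, to care that is strengthened in both arms.

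**Conclusion.** The concern holds within limits. The facility effect is not identified by the comparison as stated, because the article describes no unstrengthened comparator and itself places spillover in the villages used for the estimate. The statement that spillover is captured by the comparison trend is wrong as a safeguard: spillover that improves control practices biases the between-arm effect toward the null. The Randomization and Discussions sections need reconciling.

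The size of the bias cannot be derived from the documents. Under the assumed trends and spillover above, the spurious facility effect runs from 0 to 15 points. No stated figure in the protocol is wrong on this account. Apart from dilution by spillover, the randomised primary comparison is unaffected. This should be corrected, but it does not threaten the trial's main result.

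**What to change.** 1. **Data analysis and Additional analyses.** Describe the result as change over time in control villages. Add that facility strengthening, secular trend and spillover from intervention villages cannot be separated, and that no causal conclusion will be drawn about facility strengthening alone.
2. **Randomization.** Replace the statement that spillover is captured as a secular trend with one saying that it biases the between-arm effect toward the null.
3. **Randomization and Discussions.** Give one consistent statement of the expected contamination, separating CHW visits to control women, word of mouth, and movement of women between arms.
4. **Supporting check.** Tabulate the CHW-exposure item, already in the interview, for women in control villages, and note that it will miss word-of-mouth spillover.

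The cost is a few sentences and one table from data already to be collected. The sample size and the randomised analysis do not change. What is lost is the claim about facility strengthening alone.

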### Home visits by CHWs

Five home visits by CHWs to pregnant women and their babies form the core component of the UNEST study. Two visits are conducted during pregnancy and three during the first week after delivery. The timing and focus of each visit is summarized in Table 1. During the visits, efforts are made to dialogue with the mother, husband and all key people in the family likely to be involved in the pregnancy, delivery and/or postnatal care of the mother and the baby (that is, a family approach).

**Table 1 T1:** Proposed actions during home visits by community health workers

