### Hypothesis testing

The primary analysis for each outcome will be intention-to-treat, which will be defined by a woman’s village of residence. All analyses will account for the cluster-randomized design using random effects logistic regression and will be carried out both with and without adjustment for potential confounders. The estimated effect of the intervention will be presented as a relative risk together with a 95% confidence interval (CI). Logistic regression will be used to explore whether the hypotheses stated below are true or not, and each will be adjusted for intraclass correlation (ICC), coefficient of variation (k), socio-economic status and other potential confounders. The hypotheses are that: the intervention increases

1. % of pregnant women attending ANC at least four times (from 40% to 60%)

2. % of pregnant women who get a skilled attendance at delivery (from 30% to 50%);

3. % of mothers and babies who receive postnatal care (from 12% to 50%).

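### The total-visit groups in the secondary exposure analysis do not order women by antenatal visits, and the timing split beside them only partly repairs this

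*Protocol article*

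**What the plan says.** The section *Home visits by CHWs* fixes the schedule: "Two visits are conducted during pregnancy and three during the first week after delivery".

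The section *Additional analyses* plans an analysis "taking account of the quality of the intervention received, as assessed by the process indicators and number of visits received". It notes that women are mobile, that "some women will move from their place of residence" to relatives' homes for delivery, and that movement between arms may be considerable. It continues: "Thus we will also compare outcomes subdividing women and newborns into the following groups". Two groupings follow in that sentence:

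- by timing: "whether the visits were only pre-delivery or only post-delivery or both";
- by total number: "whether the woman received all five visits, only four, three or two or less visits".

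Neither grouping is limited to particular outcomes. The text does not say that the two are crossed. The same paragraph keeps intention to treat as the main analysis.

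*Hypothesis testing* names three outcomes: at least four antenatal care (ANC) visits, skilled attendance at delivery, and postnatal care. The first two are settled by the time of delivery. So is birth preparation, which is listed under *Primary outcomes*.

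**The concern.** A visit made after birth cannot change how often a woman attended ANC, whether she prepared for birth, or who attended her delivery. For these outcomes the relevant exposure is the number of antenatal home visits: 0, 1 or 2. The total-visit groups add postnatal visits to that number and put 0, 1 and 2 visits into one group.

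A woman who had both antenatal visits and then left the village to deliver, so missing the postnatal visits, has the full relevant exposure but falls in the lowest group. A woman with no antenatal visit and three postnatal visits has none of it, yet falls in the group above. The section was written with movers in mind, so the first case is one that the authors themselves expect.

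At stake is the reading of one exposure analysis in a trial meant to inform scale-up of a five-visit package. Differences between total-visit groups in ANC attendance or skilled attendance would be hard to attribute to the antenatal visits.

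**Working it through.** The plan gives no figure to reproduce here, so the check is an enumeration.

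**Inputs.** Antenatal visits a = 0, 1, 2 and postnatal visits p = 0, 1, 2, 3 (*Home visits by CHWs*). The two groupings come from *Additional analyses*. There are 3 × 4 = 12 patterns (a, p).

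**Step 1: total-visit groups.**

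| Group | Patterns (a, p) | Antenatal counts present |
|---|---|---|
| five | (2,3) | 2 |
| four | (1,3), (2,2) | 1, 2 |
| three | (0,3), (1,2), (2,1) | 0, 1, 2 |
| two or less | (0,0), (0,1), (0,2), (1,0), (1,1), (2,0) | 0, 1, 2 |

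**Step 2: ordering.** Twelve patterns make 12 × 11 / 2 = 66 pairs. Pairs with equal a number 3 × 6 = 18, which leaves 48 that differ in antenatal count.

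- Tied (same group): 11 within two-or-less, 3 within three and 1 within four, total 15.
- Reversed: (1,0), (1,1) and (2,0) each fall below (0,3); (2,0) falls below (1,2) and (1,3); (2,1) falls below (1,3). Total 6.
- Correct: 48 − 15 − 6 = 27.

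These are counts of patterns. The protocol gives no expected frequencies, so they are not proportions of women.

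**Step 3: the timing split alone.** Post-only women all have a = 0. Pre-only and both each contain a = 1 and a = 2. Pattern (0,0) fits none of the three named groups.

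**Step 4: both splits crossed (not stated in the plan).**

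| Cell | Patterns | Antenatal counts |
|---|---|---|
| pre-only, two or less | (1,0), (2,0) | 1, 2 mixed |
| both, two or less | (1,1) | 1 |
| both, three | (1,2), (2,1) | 1, 2 mixed |
| both, four | (1,3), (2,2) | 1, 2 mixed |
| both, five | (2,3) | 2 |
| post-only, two or less | (0,1), (0,2) | 0 |
| post-only, three | (0,3) | 0 |
| no named timing group | (0,0) | 0 |

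Of the eight patterns with at least one antenatal visit, six lie in mixed cells.

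**Step 5: what the timing split can show.** Assume, for illustration only, that the 40% to 60% ANC target is the effect in fully visited women and is linear: ANC4+ = 40 + 10a. Assume also that each antenatal visit is made independently with probability q. Any antenatal visit versus post-only is then 10 × 2q / (1 − (1 − q)²).

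- q = 0.5: 10 × 1.0 / 0.75 = 13.3 points.
- q = 0.9: 10 × 1.8 / 0.99 = 18.2 points.

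So the split would reveal an antenatal effect. It averages a 10-point effect (one versus none) with a 20-point effect (two versus none) without telling them apart.

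**Step 6: postnatal practices.** The four-visit group holds (1,3), with a complete postnatal schedule, and (2,2), with an incomplete one.

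**The case against.** The strongest reply is that the total-visit grouping does not stand alone. The timing split in the same sentence puts the mover with two antenatal visits in pre-only, and the woman with three postnatal visits in post-only. This stands, and it rules out two stronger readings.

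- A reader might infer that the plan cannot tell fully exposed women from never-visited ones. That holds only within the total-visit grouping.
- A reader might use the five versus two-or-less contrast to measure the damage. Under the Step 5 model it is 20 × (1 − m) points, where m is the share of the lowest group with both antenatal visits and the rest were never visited, so anything from 0 to 20. That range ignores the timing split and does not describe what the planned analysis can show.

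Second, the analysis also draws on the process indicators, and Table 3 includes pregnant women seen once and seen twice. These are aggregate percentages. They show that the counts are available but do not redefine the groups into which individual women are placed.

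Third, *Data analysis* defers the detailed plan, and coding of exposure categories usually belongs there. This would answer a silence, but the article states the cut-points. The missing zero group and the uncrossed splits would alone be left to the detailed plan; the total-visit rule is fixed here.

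Fourth, a total count is more defensible for postnatal outcomes. Seven of the twelve listed primary outcomes are postnatal, and the antenatal visits also counsel on newborn care. This stands, and it confines the main point to delivery-settled outcomes. Nor does the plan promise a trend test, so the misordering matters only if the groups are read as a gradient. The pooling matters either way.

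**Conclusion.** The point holds in a limited form. For outcomes settled by delivery, the total-visit groups do not order women by the visits that can act. The timing split is a partial remedy that still leaves one and two antenatal visits together and gives never-visited women no named group, and crossing the splits does not remove the mixing.

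The enumeration rests only on the stated schedule and groupings. The 13.3 to 18.2 points rest on the assumed linear effect and independent visits, and serve only to show that the timing split retains information.

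Severity is minor. A reader might infer that the trial's effect estimates are at risk; they are not, because the primary analysis is by village of residence and uses no visit count. The exposure comparison is non-randomised and would need cautious reading under any grouping.

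**What to change.** In *Additional analyses*, replace the total-visit groups with two counts: antenatal visits (0, 1, 2) and first-week postnatal visits (0, 1, 2, 3).

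- For ANC attendance, birth preparation and skilled attendance, compare by the antenatal count only, with never-visited women identifiable as their own group.
- For postnatal practices, compare by the postnatal count, with the antenatal count as a second factor.
- Keep the all-five group as a description of full delivery of the package.
- Label the analysis as non-randomised.

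The cost is a sentence and one derived variable. No new data are needed: *Process documentation and monitoring* says the CHW register records home visits in pregnancy and after birth, and the planned groupings already draw on visit numbers and timing. The drawback is sparse cells. If each antenatal visit is made independently with probability 0.9, only 0.1 × 0.1 = 1% of women have none, so a two-versus-none contrast would have a very small reference group. Cell sizes should be reported with the results.
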